**1.- BACKGROUND AND RATIONALE**

**1.1 BACKGROUND**

Coronaviruses are an important group of pathogenic viruses for humans and other animals. At the end of 2019, a new type of coronavirus was identified, SARS-CoV-2, following an outbreak of pneumonia in Wuhan City, Hubei Province, China. The disease caused by SARS-CoV-2 has been called Coronavirus Disease 2019 (COVID-19), and the outbreak turned rapidly into an epidemic that spread through China and across the rest of the world, with cases having been described in all the continents except Antarctica (1). To date, there is no effective evidence-based treatment for COVID-19. Hence, treatment recommendations are based on clinical experience and pilot studies with small numbers of patients, considerable methodological weaknesses and several schools of thought.

The focus in the search for new treatments for COVID-19 has been on antiviral drugs and vaccines. Current data suggest that the disease has three stages (Figure 1): an early infection phase related to the viral response (stage I), lasting 5 to 7 days; a pulmonary phase (stage II), up to 10 to 12 days after the onset of symptoms; and finally, in a subgroup of patients, a hyperinflammation phase (stage III), consisting of cytokine release syndrome that tends to lead to acute respiratory distress syndrome (ARDS), invasive mechanical ventilation almost always being required to keep the patient alive, as well as to other complications such as hemophagocytic and antiphospholipid antibody syndromes (2, 3).

The main cause of death in COVID-19 is acute respiratory failure secondary to ARDS, triggered by the viral infection in the hyperinflammation phase (4). It is known that both the innate and adaptive immune systems are involved in this response, leading to T-cell activation and differentiation and the release of type 1 interferons and pro-inflammatory cytokines (IL-1, IL-6, IL-8, IL-21, TNF-β and MCP-1), among other immune mediators (5).

During the previous pandemics caused by coronaviruses (severe acute respiratory syndrome [SARS] and the Middle East respiratory syndrome [MERS]), glucocorticoids were not among the recommended evidence-based treatments, as it seemed that they could be associated with a poorer course of the disease (6). In line with this, the World Health Organisation (WHO) advised against the use of glucocorticoids in the treatment of SARS-CoV-2, given that some studies found these drugs to be associated with a delayed viral clearance, psychosis, complications related to diabetes mellitus, avascular necrosis and even a higher risk of mortality (7).

Despite this recommendation by the WHO, given the poor response to antiviral drugs and growing data on the cytokine release syndrome in COVID-19, the medical community has started to prescribe glucocorticoids empirically in the early inflammatory stage of the disease. Their use in real clinical practice has been supported by more recent publications suggesting that glucocorticoids do benefit patients without significant adverse effects or delayed viral clearance (8, 9), and in Spain, by the inclusion of these drugs in the majority of hospital protocols for COVID-19. Nonetheless, the level of evidence available leaves many questions unanswered, that are difficult to address outside of a comparative clinical trial.

From the molecular point of view, pulsed glucocorticoids over 3 to 5 days at high doses (from 100 mg/day of prednisone or equivalent) work through dual (genomic and non-genomic) mechanisms of action with a low risk of toxicity. That is, as well as strong genomic effects following the complete saturation of the cytosolic glucocorticoid receptors (GRs) and their subsequent translocation into the cell nucleus, high doses lead to non-genomic effects mediated by selective membrane receptors (10). These additional non-genomic effects are associated with strong clinical response that is rapid, as it does not depend on the process of nuclear translocation of the glucocorticoid-GR complex and modulation of gene expression. On the other hand, the majority of adverse events related to glucocorticoids, including infections, are dose- and time-dependent, and hence tend to be associated with long-term maintenance treatments at doses under 100 mg/day of prednisone or equivalent that only activate the genomic pathway.

Given all this, the objective of this study was to assess the safety and efficacy of pulsed glucocorticoids in the inflammation phase (stage II) of COVID-19 for modifying the clinical course of the disease, need for mechanical ventilation, intensive care unit (ICU) admission and mortality.

**Figure 1. Phases of COVID-19**

**
[figure not shown]
**

Reprinted from The Journal of Heart and Lung Transplantation, Vol 39/Issue 5, Siddiqi HK, Mehra MR, "COVID-19 illness in native and immunosuppressed states: A clinical-therapeutic staging proposal", pages 405-407, Copyright (2020), with permission from Elsevier.

**1.2 RATIONALE**

Currently, there is a compelling need for drugs with evidence-based efficacy and safety in patients with COVID-19. The need is particularly acute in patients with severe pneumonia in which cytokine release syndrome is triggered, as their prognosis is poor if there is a delay in starting treatment. In the context of health services being overwhelmed by excessive demand for intensive care and a limited availability of interleukin inhibitors, glucocorticoids are seen as a promising treatment option, and moreover, they are familiar to most practicing physicians. The aim of this study was to assess the safety and efficacy of glucocorticoids in COVID-19 pneumonia in the inflammation phase, specifically seeking to reduce ICU admissions, the need for mechanical ventilation and mortality.

**2.- HYPOTHESIS**

In patients with COVID-19 pneumonia in the inflammation phase (stage II), treatment with pulsed glucocorticoids is able to reduce the rate of treatment failure and other complications compared to the standard treatment.

**3.- OBJECTIVES**

**3.1 PRIMARY OBJECTIVE**

To assess the efficacy of pulsed glucocorticoids during the inflammation phase of the pneumonia caused by the SARS-CoV-2 virus.

**3.2 SECONDARY OBJECTIVES**

To compare

- 28-day mortality
- the proportion of patients admitted to the ICU at 28 days
- the proportion of patients requiring rescue therapy with tocilizumab at 14 days
- the length of hospital stay in days
- changes in laboratory parameters, namely, levels of C-reactive protein (CRP), interleukin 6 (IL-6), ferritin and D-dimer (DD)
- the proportion of patients experiencing serious adverse events
- the proportion of patients with bacterial, fungal and opportunistic infections
- viral clearance as assessed by nasopharyngeal PCR.

**4.- METHODS**

**4.1 STUDY DESIGN**

This is to be a phase 3 double-blind parallel-group randomised clinical trial:

1. Experimental group: standard of care + pulsed glucocorticoids versus
2. Control group: standard of care

The standard of care will consist of the treatment provided following the standard protocol at the time in the hospital. This may be updated during the course of the study.

**4.2 DISEASE/CONDITION**

Pneumonia due to SARS-CoV-2 virus (COVID-19).

**4.3 CONTEXT AND DURATION OF THE STUDY**

For this study, we will invite consecutive patients with a diagnosis of pneumonia caused by SARS-CoV-2 (COVID-19) to participate, recruiting them in the emergency department or on a hospital ward.

The study was originally conceived in the Hospital Complex of Navarra, but it was envisaged that other centres would be able to join the study, at the discretion of the study coordinator, and it has been extended to Hospital Moisès Broggi (Sant Joan Despí, Barcelona), researchers from this second hospital having been involved in the development of this version of the study protocol.

Each patient will be followed up throughout their stay on a hospital ward and to at least 28 days after the date of randomisation, any patients discharged from hospital earlier being contacted by phone. Patients will be censored when they reach the primary endpoint, are lost to follow-up or die. Patient recruitment will finish when we reach a fixed sample size. It is expected that patients will start to be included and followed up as of April 2020 and that follow-up will be completed in May 2020 [In fact, recruitment began on 28 May 2020 and is expected to be completed by February 2021]. Interim analysis of the results is due to be performed when recruitment reaches 50% of the fixed sample size.

**4.4 STUDY SUBJECTS**

The sample is to be selected from all patients who require hospital admission with a diagnosis of pneumonia due to SARS-CoV-2 based on reverse-transcription polymerase chain reaction (RT-PCR) of nasopharyngeal swabs or sputum in accordance with the recommendations of the Spanish Ministry of Health.

To be eligible, all patients must meet all the inclusion criteria and none of the exclusion criteria.

**Inclusion criteria:**

- Age ≥18 years
- Diagnosis of SARS-CoV-2 pneumonia confirmed by RT-PCR of nasopharyngeal swabs or sputum in accordance with the recommendations of the Spanish Ministry of Health
- History of symptoms compatible with COVID-19 ≥ 7 days
- At least one of the following: level of CRP >60 mg/L, IL-6 > 40 pg/ml and/or ferritin >1000 μg/L
- Provision of written informed consent.

**Exclusion criteria:**

- Allergy or contraindication to the drugs under study
- Signs of respiratory failure: SpO_2_ in ambient air < 90% or PaO_2_ in ambient air < 60 mmHg or PaO_2_/FiO_2_ < 300 mmHg
- Need for glucocorticoids or other immunosuppressants (including biologics) for another indication
- Decompensated diabetes mellitus
- Uncontrolled hypertension
- Psychotic or manic disorder
- Active cancer
- Pregnancy or breastfeeding
- Clinical or biochemical (procalcitonin > 0.5 ng/mL) suspicion of active infection with any pathogen other than SARS-CoV-2
- Management as an outpatient
- Conservative or palliative management
- Participation another clinical trial
- Any other major uncontrolled medical, psychological, psychiatric, geographic, or social problem contraindicating patient’s participation in the study or that hinders proper patient follow-up and adherence to the protocol and the evaluation of study outcomes.

**Criteria for study withdrawal:**

In accordance with the current version of the Declaration of Helsinki and legislation, patients have the right to withdraw from the study at any point and for any reason, without it affecting the medical care received by their doctor and/or referral hospital in the future. Any patients withdrawn will not be eligible for future inclusion in the study again.

Patients may be withdrawn from the study for any of the following **criteria for withdrawal:**

- Withdrawal of consent by the patient and/or refusal of treatment and/or lack of cooperation
- Toxicity, adverse events, or intercurrent illness that, in the opinion of the researcher, warrant withdrawal
- Development of any exclusion criteria which could be clinically relevant and affect patient´s safety or non-compliance with the protocol
- Decision of the principal investigator, if withdrawal from the study would be in the patient´s interests.

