**5.- OUTCOME MEASURES**

5.1 PRIMARY ENDPOINT

Proportion of patients with treatment failure up to 14 days after randomisation.

Definition of treatment failure:

1. Patient death or
2. ICU admission or
3. Start of mechanical ventilation or
4. Clinical worsening, defined as:
   - Decrease in PaO_2_ by ≥15% from baseline + laboratory or radiological progression or
   - SpO_2_ in ambient air falling to < 90% or PaO_2_ in ambient air to < 60 mmHg or PaO_2_/FiO_2_ < 300 mmHg.

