**6.2 STATISTICAL ANALYSIS**

Initially, univariate descriptive analysis will be performed: calculating measures of central tendency and dispersion (means, standard deviation and confidence intervals or median and interquartile range depending on the distribution of the data) for continuous variables and frequencies for qualitative variables with their corresponding confidence intervals for the overall rates. Kolgomorov-Smirnov tests will be used to assess whether the continuous data follow a normal distribution and therefore parametric tests can be used.

Subsequently, it will be assessed whether randomisation achieved balance between the two arms: comparing the means of quantitative variables using Student’s t or the Mann-Whitney U tests, as appropriate, and qualitative variables using the chi-squared test or Fisher´s exact tests. If the desired balance is achieved, the primary endpoint will be compared between the groups to test the null hypothesis (H0) that the proportions are equal, assuming that the statistic for assessing the differences follows a normal distribution with a mean of 0 and standard deviation of 1; otherwise, multivariate analysis will be performed using logistic regression to assess the risk of treatment failure, estimating the effect of the intervention as an odds ratio with the corresponding 95% confidence interval.

The analysis will be performed on an intention-to-treat basis

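### The withdrawal criteria let patients leave the study, not only the study drug, for outcome-related reasons, so day-14 status and 28-day outcomes can go uncollected

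*Protocol*

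**What the plan says.** **Withdrawal (section 4.4).** The rule opens with "Patients may be withdrawn from the study for any of the following" criteria. It is permissive, and it concerns the study, not only the infusion. Apart from withdrawn consent, refusal or lack of cooperation, the grounds are:

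- harm or another illness, given as "Toxicity, adverse events, or intercurrent illness that, in the opinion of the researcher, warrant withdrawal";
- a change in eligibility, given as "Development of any exclusion criteria which could be clinically relevant", with the proviso that it bears on the patient's safety; the same ground also covers failure to comply with the protocol;
- a decision by the principal investigator in the patient's interest.

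Nothing says that outcome collection continues after any of these.

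**Exclusion criteria (section 4.4).** One criterion reads "Signs of respiratory failure: SpO_2_ in ambient air < 90% or PaO_2_ in ambient air < 60 mmHg or PaO_2_/FiO_2_ < 300 mmHg". Others cover diabetic decompensation, hypertension that is not controlled, psychosis or mania, and suspected infection with another organism.

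**Primary endpoint (section 5.1).** One limb of clinical worsening is "SpO_2_ in ambient air falling to < 90% or PaO_2_ in ambient air to < 60 mmHg", followed by the same PaO2/FiO2 limit of 300 mmHg.

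**Analysis (section 6.2).** "The analysis will be performed on an intention-to-treat basis".

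**The concern.** Each exclusion criterion becomes, through the withdrawal rule, a possible reason to leave the study. Several of them describe what the trial is meant to measure: respiratory deterioration and glucocorticoid toxicity. Leaving the study can therefore depend on how the patient is doing.

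It can also depend on arm. The plan expects more deterioration on placebo (35% failure against 10%, section 6.1), while glucocorticoid toxicity would be expected mainly on methylprednisolone. The two routes can push in different directions:

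- If placebo patients leave after respiratory failure and later deaths are missed, control mortality is understated.
- If methylprednisolone patients leave early with toxicity and would have gone on to fail, failure on methylprednisolone is understated.

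The documents do not allow a net direction to be predicted. Data that were never collected cannot be restored by the analysis.

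**Working it through.** This is mainly a comparison of texts. The plan gives no withdrawal rate, so it has no figure of its own to reproduce.

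**Step 1. Respiratory limits.** The exclusion criterion and the second limb of clinical worsening use the same three values: SpO2 below 90%, PaO2 below 60 mmHg, PaO2/FiO2 below 300 mmHg. Death, ICU admission, mechanical ventilation and the limb based on a 15% fall in PaO2 are not exclusion criteria. The overlap is with one limb of the composite.

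**Step 2. Safety events.** The list of glucocorticoid-related events under Independent variables names seven, apart from others.

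| Named safety event | Counterpart among exclusion criteria |
|---|---|
| Diabetes decompensation | yes |
| Infection (also a secondary endpoint) | yes, suspected other infection |
| Psychosis or mania | yes |
| Hypertension worsening | overlaps |
| Dyspepsia | no |
| Gastrointestinal haemorrhage | no |
| Delayed viral clearance | no |

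Four of seven match or overlap.

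**Step 3. What other sections presume.** Section 4.3 follows every patient to at least day 28. Section 5.3 gives rescue treatment in both groups at the same respiratory limits (where no other condition explains them), and receipt of that rescue is a secondary endpoint. Section 6.2 analyses by intention to treat. All three take these patients to be still in the trial. Section 4.3 also says that patients are censored on reaching the primary endpoint and does not mention withdrawal, which leaves follow-up after failure less clear.

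**Step 4. What can be lost, by route.**

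| Route out of the study | Day-14 failure status | 28-day mortality and ICU admission | Safety |
|---|---|---|---|
| Respiratory limit crossed by day 14 | known: failure | can be lost | later events can be lost |
| Toxicity, another developed exclusion criterion or investigator decision before day 14, no failure yet | can be lost | can be lost | trigger recorded; later events can be lost |
| Any reason after day 14 | known | can be lost | later events can be lost |

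**Step 5. Sensitivity to lost outcomes.** Inputs from section 6.1: 30 per arm, failure 35% and 10%, 72 recruited.

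- Planned failures: 30 × 0.35 = 10.5 and 30 × 0.10 = 3.
- One unknown status in an arm of 30: 1/30 = 3.3 percentage points.
- The plan's 72 is 60 × 1.2, or 36 per arm, which leaves room for 6 unknown per arm. Assume, purely to show the range, that 6 of 36 are unknown in each arm and that the other 30 follow the planning rates. The difference in failure then lies between (10.5 − (3 + 6))/36 = 1.5/36 = 4.2 points and ((10.5 + 6) − 3)/36 = 13.5/36 = 37.5 points, around the planned 25.

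These are outer limits. The allowance of 6 covers losses of every kind and is not a forecast of withdrawals. Whether the sample size of 60 is itself adequate does not affect this point.

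**The case against.** The case on the other side is substantial, and most of it stands.

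**Primary events are withdrawn instead of counted.** A reader might infer this from the shared limits. The documents do not support it. A patient who crosses a limit by day 14 has met the binary endpoint at that moment, and an intention-to-treat analysis counts it. Withdrawal is optional and carries a safety qualifier. That qualifier would hardly screen out respiratory failure, but nothing directs that a recorded failure be removed.

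**Safety events disappear.** Also too strong. Section 7.1 has all adverse events recorded and followed until they resolve or are judged permanent, and section 7.2 requires serious events to be reported within 24 hours. The triggering event is on file; only events after withdrawal are exposed.

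**The rule contradicts intention to treat.** Permitting withdrawal does not by itself contradict analysis by allocation. How withdrawn patients are counted may properly be left to an analysis plan that is not shown.

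**The bias can be calculated.** Suppose a share w of all failures were dropped in each arm, so that observed failure is p(1 − w)/(1 − pw). With w of 10%, 20% and 30%, the 25-point difference falls to 23.6, 21.9 and 20.2 points. These shares have no source, and they apply to every failure component although only one limb overlaps. They are also equal across arms, which leaves the odds ratio untouched: (0.35/0.65)/(0.10/0.90) = 4.85, and at w = 20%, (0.28/0.65)/(0.08/0.90) = 4.85. The odds ratio is the only effect measure that section 6.2 names. The exercise does not measure the problem here.

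**What remains.** Neither the intention-to-treat statement nor an analysis plan can supply outcomes that nobody collected. Whether follow-up continues after withdrawal is a matter for the protocol, and the protocol permits departure from the study without saying that it does.

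**Conclusion.** The concern holds in a limited form. The protocol does not separate stopping study drug from leaving the study, and it permits the latter on grounds related to the outcomes. At risk are 28-day mortality, 28-day ICU admission and later infections and serious adverse events in anyone withdrawn, and the day-14 status of patients withdrawn early for non-respiratory reasons. The loss may differ by arm.

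Its size cannot be stated. It depends on how often investigators use the discretion and on whether sites go on collecting data regardless; the documents are silent on both. The arms are small enough for a few lost outcomes to matter, at 3.3 points each with 30 per arm. Differential loss by arm is plausible from the planning rates and the drug's expected toxicity, but it is not established.

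**What to change.** Amend the withdrawal criteria in section 4.4 as follows:

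1. Separate stopping study drug from leaving the study.
2. State that, unless the patient withdraws consent for follow-up, outcome and safety data are collected to day 28 for every randomised patient, whatever happens to study drug.
3. State that meeting the respiratory limits is recorded as treatment failure and is not a reason to end follow-up.
4. State that all randomised patients stay in the intention-to-treat analysis.

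Then reconcile the exclusion and withdrawal criteria (4.4), follow-up and censoring (4.3), the primary endpoint (5.1), the rescue passage (5.3) and the analysis statement (6.2), so that all describe the same patients as still under observation. No rule on treating patients or stopping treatment needs to change.

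The cost is a wording amendment. Follow-up can use the hospital records and the telephone contact already planned.

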**5.- OUTCOME MEASURES**

5.1 PRIMARY ENDPOINT

Proportion of patients with treatment failure up to 14 days after randomisation.

Definition of treatment failure:

1. Patient death or
2. ICU admission or
3. Start of mechanical ventilation or
4. Clinical worsening, defined as:
   - Decrease in PaO_2_ by ≥15% from baseline + laboratory or radiological progression or
   - SpO_2_ in ambient air falling to < 90% or PaO_2_ in ambient air to < 60 mmHg or PaO_2_/FiO_2_ < 300 mmHg.

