**5.3 INTERVENTION**

During the randomisation, patients with be randomly allocated to the experimental or control group (Figure 2):

- 1. Experimental group: standard of care at the discretion of the researcher, including lopinavir/ritonavir (200/50 mg orally, 2 tablets q12h for 7 to 14 days) ± remdesivir (200 mg loading dose intravenously on day 1, followed by 100 mg/day for 5 to 10 days), or no drug treatment, plus pulsed methylprednisolone (120 mg/day intravenously on days 1, 2 and 3).
  2. Control group (standard): standard of care at the discretion of the researcher, including lopinavir/ritonavir (200/50 mg orally, 2 tablets q12h for 7 to 14 days) ± remdesivir (200 mg IV on the first day, followed by 100 mg/day for 5 to 10 days), or no drug treatment, plus placebo* (intravenously on days 1, 2 and 3).

*Note: placebo consists of 100 ml of 0.9% sodium chloride.

The doses of methylprednisolone (120 mg IV) or placebo (NaCl 0.9% IV) will be prepared and dispensed by the hospital pharmacy. Only the staff responsible for preparing the medication will know patient group allocation. That is, neither the researcher nor nurses administering the treatment will know the content of the bags supplied.

Patients in both groups will be treated with tocilizumab if at any point the following are observed:

- Decrease in PaO_2_ ≥15% from baseline + laboratory or radiological deterioration and/or
- SpO_2_ in ambient air falling to < 90% or PaO_2_ in ambient air < 60 mmHg or PaO_2_/FiO_2_ below 300 mmHg not explained by any other condition.

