**5.4.2 Follow-up**

During hospital admission, patients will be followed-up in accordance with standard procedures for COVID-19 (11), with close monitoring of their vital signs (temperature, blood pressure, heart rate, respiratory rate, and oxygen saturation). All patients in the study will be assessed in person at least once a day by a doctor who is a member of a specialized COVID-19 team, in accordance with the established treatment protocol. The detection of any significant clinical change will prompt an addition assessment of vital signs and medical examination.

Blood tests involving a blood count, coagulation tests including D-dimer, and the measurement of renal function and levels of CPR, procalcitonin, ferritin, LDH and IL-6, will be performed every 48 hours and whenever there is a significant clinical change, at the discretion of the doctor in charge. Further, a chest X-ray will be performed every 48 hours and in the event of a significant clinical change, at the discretion of the doctor in charge, and the results will be interpreted by a pulmonary radiologist.

A follow-up RT-PCR will be performed before administrative discharge and this is to be performed at least 7 days after the first PCR.

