**6.- STATISTICS**

**6.1 SAMPLE SIZE**

It was estimated that 60 patients (30 in each arm) were needed to detect as significant (two-tailed type I error of 0.05 and a type II error of 0.2) an absolute difference of 25% in the primary endpoint between the groups: 35% in the control group and 10% in the intervention group. Assuming a loss to follow-up of 20%, it is necessary to recruit a total of 72 patients.

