**APPENDIX IN RESPONSE TO THE MEASURES TAKEN BY THE SPANISH AGENCY OF MEDICINES AND MEDICAL DEVICES (AEMPS) REGARDING CLINICAL TRIALS OF HYDROXYCHLOROQUINE FOR COVID-19**

After the notification received by the researchers of the CORTIVID trial (EudraCT number: 2020-001827-15, Name of sponsor: Navarrabiomed-Fundación Miguel Servet) on 15 July 2020 and in accordance with the measures adopted by AEMPS on 22 June 2020 regarding clinical trials of hydroxychloroquine in COVID-19, the use of this drug in the CORTIVID trial was halted, as was the recruitment of patients on the drug. The design of the trial was modified accordingly, by amendment of the protocol to that detailed in this document.

The trial is currently in the active recruitment stage, with five patients having been included across two hospitals. [At the time of submission of this protocol for publication, 46 patients have been recruited and analysis is ongoing.]

We consider that the CORTIVID trial continues to be warranted and remains relevant in the current circumstances for the following reasons: 1) use of an active ingredient (methylprednisolone) and a different regimen (short three-pulse regimen) from that used in the RECOVERY trial; 2) research into the efficacy and safety of glucocorticoids in a clinical scenario that also differs from that considered in the RECOVERY study (patients with SARS-CoV-2 pneumonia not requiring oxygen but with poor prognostic factors); and 3) the possibility of confirming some of the findings of the RECOVERY trial in a double-blind randomized placebo-controlled study.

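### The 15% PaO2 limb of treatment failure does not fix the oxygen condition, so starting oxygen can hide a true fall while PaO2/FiO2 stays at 300 or above

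*Protocol*

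**What the plan says.** Clinical worsening in the Protocol, section 5.1 Primary endpoint, has two limbs.

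- Relative limb: "Decrease in PaO_2_ by ≥15% from baseline + laboratory or radiological progression". No oxygen condition is given for the baseline or the later value.
- Absolute limb: "SpO_2_ in ambient air falling to < 90% or PaO_2_ in ambient air to < 60 mmHg or PaO_2_/FiO_2_ < 300 mmHg". Each value is tied to ambient air or divided by FiO2.

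The exclusion criteria (section 4.4) are built like the absolute limb: "Signs of respiratory failure: SpO_2_ in ambient air < 90% or PaO_2_ in ambient air < 60 mmHg or PaO_2_/FiO_2_ < 300 mmHg". Section 5.3 Intervention repeats the relative limb as a trigger for tocilizumab, again with no oxygen condition: "Decrease in PaO_2_ ≥15% from baseline + laboratory or radiological deterioration".

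The Appendix on the AEMPS measures describes the population as "patients with SARS-CoV-2 pneumonia not requiring oxygen but with poor prognostic factors". No inclusion or exclusion criterion requires the patient to be breathing air at baseline, and nowhere is the oxygen condition of the baseline PaO2 stated.

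**The concern.** PaO2 depends on the inspired oxygen as well as on the lungs. A percentage change between two raw values measures gas exchange only if both were taken at the same FiO2. The absolute limb respects this and the relative limb does not.

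The case that matters most follows from the intended population. Baseline is on air, the patient worsens, oxygen is started, and the next gas is compared with a baseline taken on less oxygen. The rise from the oxygen offsets the fall from the lungs, and the limb is not met. A smaller problem runs the other way: a baseline gas on oxygen followed by one on air shows a fall that comes from the oxygen supply.

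At stake is the classification of the primary endpoint in a trial planned on 30 patients per arm. The rule as written gives an answer, and for these patients it is the wrong one, so this is more than a detail left for later.

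**Working it through.** **Inputs.** From the Protocol: the 15% fall and the PaO2/FiO2 limit of 300 (section 5.1). Assumed, because the document gives none: FiO2 of 0.21 on air, supplemental FiO2 of 0.24 to 0.32, and baseline PaO2 of 75 to 90 mmHg. PaO2/FiO2 (the ratio) is treated as an index of gas exchange that does not itself change with FiO2, which is a simplification.

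**The plan's own figures.** None exists for this limb. Section 6.1 gives only overall failure rates (35% and 10%). Its 30 per arm does not reproduce: the usual two-sided pooled formula gives 43. That is a separate matter, and nothing below rests on it.

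**Starting oxygen, baseline on air.** With baseline PaO2 b:

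- Baseline ratio = b / 0.21. After a true 15% fall it is 0.85 × b / 0.21.
- The absolute limb scores failure below 300. The hidden window therefore runs from 300 up to 0.85 × b / 0.21.
- A ratio of 300 corresponds to 0.21 × 300 = 63 mmHg on air, above the 60 mmHg limit. A window exists only if b exceeds 63 / 0.85 = 74.1 mmHg.
- At a ratio of 300, raw PaO2 on FiO2 f is 300 × f. The relative limb is missed if this exceeds 0.85 × b, that is, if f > 0.85 × b / 300.

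| Baseline PaO2 on air | Baseline ratio | Hidden window | True fall at ratio 300 | FiO2 needed to hide the whole window | Raw PaO2 change at ratio 300, FiO2 0.24 | FiO2 0.28 | FiO2 0.32 |
|---|---|---|---|---|---|---|---|
| 75 | 357 | 300–304 | 16.0% | > 0.213 | −4.0% | +12.0% | +28.0% |
| 80 | 381 | 300–324 | 21.3% | > 0.227 | −10.0% | +5.0% | +20.0% |
| 85 | 405 | 300–344 | 25.9% | > 0.241 | −15.3% | −1.2% | +12.9% |
| 90 | 429 | 300–364 | 30.0% | > 0.255 | −20.0% | −6.7% | +6.7% |

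At FiO2 0.28 the whole window is hidden in every row. At 0.24 the bottom of the window is still detected for baselines of 85 and 90.

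One patient: 90 mmHg on air (90 / 0.21 = 429), then 95 mmHg on 0.28 (95 / 0.28 = 339). Gas exchange has fallen by 21%, raw PaO2 has risen by 5.6%, and neither limb is met on these gases.

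**Returning to air, baseline on FiO2 f.** At a constant ratio the change in raw PaO2 is 0.21 / f − 1.

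- It reaches −15% at f = 0.21 / 0.85 = 0.247.
- From 0.24: −12.5%, not enough. From 0.28: −25.0%. From 0.32: −34.4%.
- With a true 10% gain in the ratio from 0.28: 0.21 × 1.1 / 0.28 − 1 = −17.5%, still past the trigger. The gain needed to avoid it is 0.85 × 0.28 / 0.21 − 1 = 13.3%.

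The exclusion removes patients with a ratio below 300. A patient on oxygen with a ratio of 300 or more can enter, so this route is open.

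**The case against.** The strongest reply is that the reach is small.

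- Hiding stops at a ratio of 300, and the window is narrow for the lower baselines (300–304 at 75 mmHg). This stands. It relies on an arterial gas, though, and sections 5.4.1 and 5.4.2 list oxygen saturation, blood tests and X-rays but no arterial gas.
- A hidden patient may still be counted within 14 days through death, ICU admission, ventilation or a later ratio below 300. This also stands. The loss is limited to patients who meet none of these but do have the laboratory or radiological progression that the limb requires.
- Figure 2 is not shown, and its legend lists PaO2 in ambient air. It may carry a condition that the text lacks. This cannot be settled, and the endpoint text should not depend on it.

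A reader might infer that taking an improving patient off oxygen is scored as failure. The document does not support that. The fall alone is not failure, because laboratory or radiological progression must also be present, which fits poorly with improvement, although progression is undefined. The baseline gas must also have been taken on oxygen, whereas the Appendix describes patients who do not need it. If baseline was on air, weaning returns the patient to the baseline condition and creates no artificial fall.

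**Conclusion.** The relative limb is badly fixed and should be corrected. Its main consequence is hidden failures when oxygen is started after a baseline on air, within the windows tabulated above and only while the ratio stays at 300 or above. Spurious failures on return to air are possible but need several conditions together. The windows rest on the assumed baseline and FiO2 values and on the ratio as a stable index of gas exchange.

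Two further inferences are tempting and unsupported.

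- **Bias against the drug.** If methylprednisolone works, treated patients may come off oxygen sooner, which would add spurious failures. They should also show less laboratory or radiological progression, which would remove them. Hidden failures would fall more on whichever arm worsens more. The net sign cannot be determined.
- **A stated loss of power.** The Protocol gives neither the share of failures expected through this limb nor the share of patients on oxygen at baseline. Any misclassification rate would be invented, and a power figure computed from it would only return that assumption.

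**What to change.** In section 5.1 Primary endpoint, define this limb as a relative fall from baseline in PaO2/FiO2, with FiO2 recorded for both gases. Alternatively, require both gases under the same oxygen condition. Either removes the artefact as modelled here. The size of the fall remains the sponsor's choice.

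The cost is one line in the definition and an FiO2 entry with each gas. FiO2 must be estimated for patients on oxygen, which brings some error, but the limb at 300 already requires it and the variable list in section 5 already includes SpO2/FiO2 at baseline and follow-up. The same-condition option avoids the estimate but leaves the limb unreadable when only gases on different oxygen are available.

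Section 5.3 currently shares the raw wording as a rescue trigger, so editing 5.1 alone would separate the two. The sponsor must reconcile the two sections; no clinical rule is proposed here. The Appendix reports 46 patients recruited and analysis under way, so any change should be made without knowledge of allocation and applied in the same way to patients already enrolled.
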